### Intervention and randomisation

Participants were randomly allocated with a 1:1 ratio to one of two treatment groups: vitamin D_3_ (cholecalciferol) 1200 IU/day or placebo. Participants were stratified by sex and women were stratified by age (60–70 years/71–80 years). An independent pharmacist prepared three randomisation lists with computer-generated numbers using block sizes of four.

The intervention group takes three tablets of 400 IU vitamin D_3_ daily for a duration of 12 months. Based on earlier research, the daily dose of 1200 IU will lead to stable mean 25(OH)D levels of >80 nmol/L in the intervention group, with 90 % of individual 25(OH)D levels above 60 nmol/L within a few months [44, 45]. The placebo group receives identical tablets without vitamin D and it is expected that this group maintains a mean serum 25(OH)D level of about 45 nmol/L. Both the vitamin D and placebo tablets were purchased from Vemedia Manufacturing B.V., The Netherlands. The tablets are supplied in vials of 100 tablets for 6 months, 600 tablets at a time. Participants are allowed to take a (multi)vitamin D supplement with a maximum of 400 IU/day in addition to the study tablets.

#### Co-intervention

Calcium positively influences the bioavailability of vitamin D [46]. In addition, some effects of vitamin D may be caused by increased calcium absorption. Therefore, all participants were advised to use at least three dairy consumptions daily to ensure adequate calcium intake of about 1000 mg/day. Calcium intake was assessed with a structured questionnaire during the screening phase. If calcium intake was low (less than 2 dairy consumptions per day), calcium tablets of 500 mg/day were prescribed to these participants.

### Study procedures

Face-to-face interviews take place at screening, baseline, six and 12 months. The baseline visit was timed closely after the screening phase. Shortly prior to the interviews, participants are asked to complete a mailed questionnaire to reduce interview time. Short telephone interviews are conducted after two weeks, three and nine months to check compliance and adverse events. Table 4 lists all measurements and their time points of the D-Vitaal study. Interviews and blood sampling are carried out by trained researchers or research nurses and take place at the participant’s home, at the VU University Medical Center, or at local community medical centres. The Endocrine Laboratory of the VU University Medical Center conducts the 25(OH)D determinations. Participants who discontinue taking the study tablets for any reason are asked to participate in the remaining follow-up measurements. Any (serious) adverse events are carefully monitored.

**Table 4 Tab4:** Assessed domains, instruments and their time points in the D-Vitaal study

		*Time point*			
Domain	Instrument	Screening	T0 (baseline)	T1 (6 months)	T2 (12 months)
Primary outcome variables:					
Depressive symptoms	CES-D	X	X	X	X
Functional Limitations	LASA-FL	X	X	X	X
	SF-36 PCS	Partly	X	X	X
Physical performance	SPPB		X	X	X
Secondary outcome variables:					
Major depressive disorder	CIDI	X		X	X
Anxiety	BAI		X	X	X
Health-related quality of life	SF-36		X	X	X
	EQ-5D		X	X	X
Cognition	Stroop test		X	X	X
Physical performance					
Mobility	TUG		X	X	X
Hand grip strength	Dynamometer		X	X	X
Health care costs	TiC-P		X	X	X
Serum 25(OH)D		X		X	
Possible covariables:					
Demographic information					
Age, sex		X			
Education level			X		
Marital status			X	X	X
Lifestyle					
Smoking behaviour			X	X	X
Alcohol consumption			X	X	X
Physical activity	LAPAQ		X	X	X
Blood pressure	Omron device		X	X	X
Anthropometry					
BMI	Height, weight		X	X	X
Waist and calf circumference	Tape measure		X	X	X
Chronic diseases	7 majors		X	X	X
Medication and supplement use			X	X	X
Predictors of vitamin D status			X	X	X
Use of counselling			X	X	X

CES-D: Centre of Epidemiological Studies Depression scale; LASA-FL: Longitudinal Aging Study Amsterdam Functional Limitations questionnaire; SF-36 PCS: Short Form 36 Health Survey - Physical Component Summary score; SPPB: Short Physical Performance Battery; CIDI: Composite International Diagnostic Interview; BAI: Beck Anxiety Inventory; EQ-5D: EuroQol 5 Dimensions; TUG: Timed Up-and-Go test; TiC-P: Trimbos and iMTA questionnaire on Costs associated with Psychiatric illness; LAPAQ: Longitudinal Aging Study Amsterdam Physical Activity Questionnaire

### Compliance

Compliance is checked by tablet count. To stimulate compliance, participants are contacted by telephone (after two weeks, three and nine months) and reminded at follow-up visits. The ultimate compliance check is the measurement of serum 25(OH)D after 6 months.

### Outcomes

#### Primary outcomes

##### Depressive symptoms

The CES-D [41] is used to measure differences in mean change of depressive symptoms after 12 months between the two treatment groups. The CES-D contains 20 items with a score range of 0–60. Higher scores indicate more depressive symptoms. A score of ≥16 is indicative of clinically relevant depressive symptoms. The CES-D is a widely used instrument that displays good psychometric properties in various elderly populations [47].

##### Functional limitations

The LASA-FL questionnaire [42] includes six items assessing common daily activities: climbing stairs, cutting toenails, walking 5 minutes outdoors without resting, rising from a chair, dressing/undressing oneself and using own or public transport. Participants indicate whether they are able to perform these activities without difficulty, with some difficulty, with much difficulty, only with help, or not at all. The instrument can be scored in two ways: by determining the amount of functional limitations (score range 0–6, with higher scores indicating presence of more functional limitations) and the degree of functional limitations (score range 0–24, with higher scores indicating more severe functional limitations). The LASA-FL is used to measure differences in mean change of the amount and degree of functional limitations after 12 months between the two treatment groups.

##### Physical performance

A modified version of the Short Physical Performance Battery (SPPB) [26, 48] is used to determine differences in mean change of objective physical performance between the treatment groups after 12 months. The SPPB includes a walking test (walking 3 meters, turning 180° and walking 3 meters back as fast as possible), a chair stands test (standing up from a chair without using hands five times as fast as possible) and a balance test (standing with feet in tandem stand (i.e. standing with one foot in front of the other, with the heel of one foot touching the toes of the other foot) for up to 30 seconds). Participants can score 0–4 points for each test, adding up to a maximum of 12 points, with higher scores indicating better performance. Reliability and validity of the SPPB are good [49].

#### Secondary outcomes

##### Incidence of MDD

The depression-section of the DSM IV-based Composite International Diagnostic Interview (CIDI, version 2.1) [50] is used to assess presence of MDD. At six and 12 months, the CIDI is administered if a participant scores ≥16 on the CES-D.

##### Anxiety

The Beck Anxiety Index (BAI) [51, 52] is a well-validated questionnaire that contains 21 items measuring anxiety symptoms that are relatively distinguishable from depression symptoms.

##### Cognition

Cognitive function is assessed with indicators of information processing speed and executive functioning obtained from the Stroop-Colour Word Test [53].

##### Health-related quality of life

Health-related quality of life is measured with the EuroQol - 5 Dimensions (EQ-5D) [54] and the SF-36 [43]. The EQ-5D is a utility instrument that enables the calculation of Quality Adjusted Life Years (QALY’s). The SF-36 Mental Component Summary score (MCS) and Physical Component Summary score (PCS) are used as a measure of mental and physical health-related quality of life, respectively [43]. Both instruments are widely used and well-validated in older populations [43, 55].

##### Timed Up-and-Go test

With the Timed Up-And-Go Test (TUG), functional mobility is assessed by asking the participant to stand up from a standard chair, walk a 3 meter distance, turn, walk back to the chair and sit down again [56].

##### Hand grip strength

Hand grip strength is measured in kilograms with a strain-gauged dynamometer (Takei TKK 5401, Takei Scientific Instruments Co. Ltd., Japan). Participants are asked to apply maximum force on the device while in a standing position. Grip strength is measured twice for each hand, consecutively alternating between both hands. The hand grip strength score is derived by taking the mean of the highest score for each hand.

##### Economic evaluation

To evaluate whether vitamin D is a cost-effective intervention for the prevention of depression and poor physical function in older persons, an economic evaluation will be performed. Dutch costing guidelines will be used [57]. All relevant costs will be measured and valued, including the costs of the vitamin D intervention. Health care utilization is measured with the Trimbos and iMTA questionnaire on Costs associated with Psychiatric illness (TiC-P) [58]. Health care costs include costs of GP and psychiatric care, ambulatory and outpatient hospital care, physical therapists and home care. Costs of production loss are not included, as the majority of the participants does not have a paid job.

#### Possible covariables

Several variables are measured during the trial to check for possible (chance-based) differences between the treatment groups. Height and weight are measured with a calibrated stadiometer and scale, respectively. Body mass index (BMI) is calculated by dividing weight (in kilograms) by height^2^ (in meters). Waist and calf circumference is assessed with a tape-measure. Blood pressure and pulse are assessed twice with a three-minute interval using the Omron M1 Plus device (Omron Healthcare Europe). The date of the baseline interview is used to measure seasonal variation of serum 25(OH)D levels [38]. Structured questionnaires assess age, gender, education level, marital status, smoking behaviour, alcohol use, current medication and supplement use, use of corticosteroids in the past three months, chronic diseases, physical activity (walking, cycling, gardening, household activities and sports [59], vitamin D predictors (exposure to sunlight, skin pigmentation, consumption of fatty fish) [60] and use of counselling.

#### Blood sampling and assessment of serum 25(OH)D

Blood samples are obtained in the morning by a trained research nurse at screening and 6 months for measurement of serum 25(OH)D. Participants are in a fasted state with regard to dairy products. Serum 25(OH)D is determined using liquid chromatography followed by tandem mass spectrometry [61]. At screening, 25(OH)D was determined immediately after blood sampling. The 25(OH)D determinations of the 6-month blood samples will be carried out at the end of the study, to ensure randomization concealment. Serum, EDTA plasma and whole blood samples are stored frozen (−80 ° C) until determination and for potential future biomarker and DNA research.

### Power calculation

The primary outcomes of the D-Vitaal study are change in depressive symptoms (CES-D score) and change in physical functioning (functional limitations and physical performance) after 12 months. In an RCT with a comparable population (older persons from the community with depressive symptoms but no MDD), the mean CES-D score was 26 (SD: 5.1) [62]. To detect a change of 0.5 SD (i.e. 2.5 points change of CES-D score), a total of 40 subjects per group is needed, assuming a power of 80 %, a two-sided alpha of .05 and an intraclass correlation coefficient (ICC) of .70 between baseline and follow-up measurements.

The SPPB score ranges from 0 to 12. A change of one point (SD: 1.5) is regarded as a meaningful change [63]. Assuming the same power, alpha and ICC as the CES-D calculation, 22 participants per group are needed.

The LASA-FL questionnaire is scored in two ways: by determining the amount (score range 0–6) and the degree (score range 0–24) of functional limitations. A change of one point in the amount of functional limitations can be regarded as a meaningful change [64]. The SD was set on 1.7, based on analyses in the Longitudinal Aging Study Amsterdam (LASA), a large prospective cohort study of older persons. Assuming again the same power, alpha and ICC as the previous calculations, at least 28 persons per group should be included. For the degree of functional limitations, no meaningful change data or RCTs could be identified in the literature. Based on analyses in LASA, a mean difference of 2 points can be expected, with an SD of 4.5. For this outcome, 48 persons per group are needed, using the same assumptions as indicated above. Considering an expected dropout of 25 % and uncertainty of the 25(OH)D assay, we aimed to include at least 70 participants per group, altogether at least 140 participants.

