### Screening phase

The screening phase of the D-Vitaal study included two steps: a mailed questionnaire and a short interview including a blood sample. The screening questionnaire assessed presence of depressive symptoms (Centre of Epidemiological Studies - Depression scale (CES-D) score of ≥16 [41]) and functional limitations and was also used to exclude persons who use antidepressant medication, vitamin D >400 IU/day and/or calcium supplements >1000 mg/day. For the first 12 participants, we used only the Functional Limitations questionnaire of the Longitudinal Aging Study Amsterdam (LASA-FL) [42] for the assessment of functional limitations. A LASA-FL score of ≥1 indicates the presence of functional limitations. However, this instrument proved not sensitive enough for this study population, creating a large ceiling effect. Especially younger-old participants (e.g. persons in their early sixties) reported few or no problems on this scale, as their level of general functioning was still moderate to high. Therefore, we added the Physical Functioning subscale of the Short Form-36 Health Survey [43] (SF-36-PF) to the screening phase. The SF-36-PF contains 10 items on physical functioning and assesses a broader range of functional limitations. Having difficulty with at least one of the items of the SF-36-PF was regarded as presence of functional limitations. Persons who were eligible according to the screening questionnaire (presence of both depressive symptoms and functional limitations) were invited for a screening visit where presence of MDD was examined and a blood sample was drawn to determine serum 25(OH)D levels.

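### CES-D and LASA-FL are measured twice before treatment, but the planned covariates do not include the screening score; adding it is an optional, modest gain in precision

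*Protocol article*

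**What the plan says.** Table 4 of the protocol article ("Assessed domains, instruments and their time points in the D-Vitaal study") marks CES-D and LASA-FL at screening, T0, 6 and 12 months. SPPB starts at T0. The table labels T0 as baseline.

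Under Screening phase, the early scores serve as an entry test: "The screening questionnaire assessed presence of depressive symptoms" with a cut of 16 on the CES-D, and functional limitations by LASA-FL, with SF-36-PF added after the first 12 participants. Study procedures says that the baseline visit followed soon after screening.

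Under primary outcomes, the CES-D "is used to measure differences in mean change of depressive symptoms after 12 months between the two treatment groups". LASA-FL amount and degree are defined in the same way. Neither definition names the starting value.

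The power calculation works by "assuming a power of 80 %, a two-sided alpha of .05" and "an intraclass correlation coefficient (ICC) of .70 between baseline and follow-up measurements", and applies these to all four scores.

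The possible covariables in Table 4 and in the section of that name do not include the screening CES-D or LASA-FL score. Data analysis specifies GEE or mixed models and adjusts for confounders where this proves necessary. It does not mention the screening scores either way.

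**The concern.** A single questionnaire score carries error specific to the day on which it was filled in. A second reading taken before randomisation therefore still helps to predict the 12-month score after T0 has been taken into account. Because it precedes randomisation, using it as a covariate does not bias the between-group contrast, even though entry to the trial was selected on it.

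The article gives the screening scores no role beyond entry. Its adjustment rule responds to confounding or chance imbalance, so a covariate whose only purpose is precision would not enter by that route. At stake is some width of the confidence intervals for CES-D and the two LASA-FL scores, from data that were already collected and should be nearly complete because entry required them.

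**Working it through.** **1. The plan's own figures.** Inputs from Power calculation: two-sided alpha .05, power 80 %, correlation r = .70, and these differences and SDs: CES-D 2.5 and 5.1; SPPB 1 and 1.5; LASA-FL amount 1 and 1.7; LASA-FL degree 2 and 4.5. For a change score with one pre-treatment value, the variance is SD² × 2(1 − r) = 0.60 SD², so

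n per group = 2 × (1.96 + 0.8416)² × 0.60 × SD² / difference².

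| Score | Computed | Rounded up | Stated |
|---|---|---|---|
| CES-D | 39.2 | 40 | 40 |
| SPPB | 21.2 | 22 | 22 |
| LASA-FL amount | 27.2 | 28 | 28 |
| LASA-FL degree | 47.7 | 48 | 48 |

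All four reproduce, so the calculation uses exactly one pre-treatment value.

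**2. Adjustment for T0 alone.** The residual variance factor is 1 − .70² = .51. This is the right comparator for an added covariate. The step from .60 to .51 belongs to T0 adjustment and is not credited to the screening score.

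**3. Adding the screening score.** Write s for the screening–T0 correlation and f for the screening–follow-up correlation. The protocol gives neither, so both are assumptions. T0–follow-up stays at .70. The residual factor is

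1 − (f² + .70² − 2 × s × f × .70) / (1 − s²).

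| s | f = .70 | Reduction from .51 | f = .60 | Reduction from .51 |
|---|---|---|---|---|
| .70 | .424 | 17 % | .486 | 5 % |
| .80 | .456 | 11 % | .506 | 1 % |
| .90 | .484 | 5 % | .505 | 1 % |

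**4. The CES-D entry cut.** The cut of 16 removes the lower part of the screening distribution. A simulation with all follow-up correlations at .70 before selection, s of .70 to .90, and the top 50 %, 20 % or 10 % of screening scores retained gives a reduction of about 3–10 %. A second simulation (cut at 16, unselected mean 8 to 26, SD 8, a common correlation of .70 or .80) gives 6–18 %. The upper end there needs a cut that removes few people and the higher correlation.

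**5. LASA-FL scores piled up at zero.** Screening phase reports a large ceiling effect, meaning many people without limitations. With 30–70 % of scores at zero on all three occasions, underlying follow-up correlations of .70 and s = .80, the simulated reduction is about 10 %. With s = .70 it is 14–16 %, and with s = .90 it is 4–5 %.

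**6. Power for LASA-FL degree, the score that sets the trial size.** The target of 70 per group less 25 % leaves about 52. The 155 enrolled less 25 % leave about 116, or 58 per group. From the t distribution:

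| Analysis | 52 per group | 58 per group |
|---|---|---|
| Change score (factor .60) | .83 | .87 |
| T0 adjustment (.51) | .88 | .91 |
| T0 plus screening (f = .70; .484 to .424) | .90 to .93 | .93 to .95 |

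At 52 per group the other three scores have power of .89 or more even by change score.

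**7. Covariate or average.** Averaging screening and T0 into the starting value of a change score gives the factor 1 + (1 + s)/2 − (f + .70). With f = .70 and s = .70 this is .45. With f = .60 it is .55, .60 or .65 for s = .70, .80 or .90, against .60 for T0 alone. The gain can vanish or reverse, whereas a fitted covariate does not have this weakness.

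**The case against.** The strongest objection is that the article states nothing wrongly here. Its sample sizes are correct, one baseline is the cautious planning choice, and an article may leave the exact covariate list to the full analysis plan. That stands, and it limits the point to an optional improvement.

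Three stronger readings are tempting, and the document does not support them:

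- A reader might infer that every effect is defined from T0 alone and that the screening score is discarded. Table 4 does label T0 as baseline, but the outcome definitions name no starting value, and Data analysis neither includes nor excludes the screening score. Use of a single value is shown for the power calculation only.
- A reader might take 83 % power for LASA-FL degree as a thin margin that this change would rescue. That figure belongs to the change score at the recruitment target. With T0 adjustment it is about 88 %, and with the 155 actually enrolled about 91 %.
- A reader might quote a 17–20 % gain as free. A 17 % variance reduction, equivalent to about 20 % more participants (.51/.424 = 1.20), needs both unstated correlations at .70 and no loss from the entry cut. Screening shortly before T0 points to a higher screening–T0 correlation, and selection at 16 weakens the screening–follow-up correlation. Both lower the gain.

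The ceiling effect reported for LASA-FL also limits what its screening score can add, although the simulation suggests that it does not remove the gain. None of these objections makes the covariate invalid; they reduce its expected size.

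**Conclusion.** The point holds as an optional efficiency gain of low priority. CES-D and both LASA-FL scores have a second pre-treatment reading that the power calculation does not use and that the covariable list and adjustment rule do not bring into the models. Relative to T0 adjustment alone, the residual variance would fall by roughly 3–10 % under plausible assumptions. That narrows a confidence interval by about 1.5–5 % (√.97 = .985; √.90 = .949). The upper end is about 17 %, and the gain is only about 1–5 % if the screening-to-follow-up correlation is .60. The result rests on the protocol's .70 between T0 and follow-up and on assumed values for the two correlations it does not report. No sample size needs to change, and no powered score falls below 80 %. The count of three out of four refers to the scores in the power calculation; Table 4 also lists SF-36 PCS under the primary outcomes.

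**What to change.** In Data analysis, state that T0 is the baseline. State also that the CES-D model includes the screening CES-D score, and that the LASA-FL amount and degree models each include the corresponding screening LASA-FL score, as prespecified fixed covariates in addition to the T0 value. Do not average the two readings into a change score. SPPB has no screening value and stays as it is. The screening–T0 correlation, and the correlation of each with follow-up pooled over arms, can be checked on blinded data to see what gain to expect.

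The cost is one sentence and one degree of freedom per model, with no new data collection. The wording should be fixed before unblinding, because covariates chosen afterwards invite doubt.

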### Data analysis

Baseline characteristics between treatment groups will be compared using Pearson Chi-square tests, independent-samples t-tests, one-way ANOVAs, or non-parametric tests. Persons who drop out will be compared to persons who complete the study. Skewed data will be transformed. Data will be analysed according to the intention-to-treat principle with longitudinal data analysis techniques (generalized estimating equation (GEE) analysis or mixed model analysis) using SPSS (SPSS Inc. Chicago, IL, USA). A double-sided *p*-value of .05 will be regarded as statistically significant. If needed, models will be adjusted for relevant confounding variables. To investigate the interrelatedness of depressive symptoms and physical functioning, these variables will be added to each other’s effect analysis in separate models. Effect modification will be investigated for age, gender and baseline serum 25(OH)D levels.

Per-protocol analyses will be performed as a secondary analysis with participants who were compliant with the study protocol (≥80 % tablet intake). As a compliance check, the improvement of vitamin D status - i.e. the number of participants with serum 25(OH)D levels over 50, 60 and 75 nmol/L - will also be analysed in secondary analyses. Finally, as a sensitivity analysis, it will be investigated whether change in serum 25(OH)D is associated with change in depressive symptoms, functional limitations and physical performance over time in the total study sample (irrespective of treatment group).

The economic evaluation will be performed from a societal perspective with a time horizon of 12 months. The analysis will be done according to the intention-to-treat principle. Missing cost and effect data will be imputed using multiple imputation according to the MICE algorithm [65]. Bias-corrected and accelerated bootstrapping with 5000 replications will be used to calculate 95 % confidence intervals around the mean difference in total costs between the two groups. Incremental cost-effectiveness ratios (ICERs) will be calculated by dividing the difference in mean total costs by the difference in mean effects on the primary outcomes (depressive symptoms, functional limitations and physical performance) between the treatment groups. A cost-utility analysis will be performed estimating the incremental costs per QALY gained. Bootstrapping will be used to estimate the uncertainty surrounding the ICERs, which will be graphically presented on cost-effectiveness planes. Cost-effectiveness acceptability curves and net monetary benefits will also be calculated. Sensitivity analyses will be performed on the most important and uncertain cost parameters.

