### Participants

Potential participants were screened for presence of clinically relevant depressive symptoms, functional limitations and low serum 25(OH)D levels (≤50 or ≤70 nmol/L in winter (October-March) and summer (April-September), respectively). In this way, we recruited a vulnerable population at high risk of subsequent mental and physical function decline. As severe 25(OH)D deficiency can be associated with bone disease [37], persons with 25(OH)D levels of <15 nmol/L were excluded and referred to their GP for treatment. In addition, persons with a current MDD diagnosis were excluded, as the aim of this study is to prevent depression. Furthermore, persons who use antidepressant medication were excluded at screening because of possible interference of antidepressants with the effect of vitamin D on depressive symptoms. Persons with sufficient concentrations of 25(OH)D (>50 or >70 nmol/L in winter and summer, respectively) were also excluded, as it was expected that the effect of supplementation in these persons would be negligible. The summer/winter cut-off difference of 20 nmol/L was based on the observation by Van Schoor et al. that the seasonal variation of vitamin D levels in two cohorts of Dutch older persons was 14–24 nmol/L [38]. The Health Council of the Netherlands advises a supplement of 800 IU/day vitamin D for institutionalized persons [39]. Therefore, only community dwelling persons were included in the trial. Table 3 lists the inclusion and exclusion criteria of the D-Vitaal study. All participants provided written informed consent prior to the start of the intervention.

**Table 3 Tab3:** Inclusion and exclusion criteria of the D-Vitaal study

Inclusion criteria:	Exclusion criteria:
- Men and women of ≥60 and ≤80 years	- Presence of major depressive disorder at screening
- Presence of depressive symptoms (CES-D ≥16)	- Use of antidepressant medication at screening
- Presence of ≥1 functional limitation	- Presence of major life-threatening illness
- Serum 25(OH)D levels ≤50 (winter) or ≤70 (summer) nmol/L.	- Vitamin D (>400 IU/day) or calcium (>1000 mg/day) supplementation
- Ability to comply with the study protocol	- Serum 25(OH)D levels <15 nmol/L.
	- Living in an institution

*CES-D*: Centre of Epidemiological Studies Depression scale

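### The per-protocol set is defined by study-tablet intake alone, so participants who exceed the protocol's own 400 IU/day cap on non-study vitamin D still count as compliant

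*Protocol article*

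**What the plan says.** Under Data analysis, the main analysis follows the intention-to-treat principle. A secondary per-protocol analysis is planned "with participants who were compliant with the study protocol", which a bracket defines as at least 80 % tablet intake. No other criterion is given. The Compliance section is in line with this: "Compliance is checked by tablet count".

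Under Intervention and randomisation there is a second rule, without distinction by arm: "Participants are allowed to take a (multi)vitamin D supplement with a maximum of 400 IU/day in addition to the study tablets". It mirrors the entry exclusion in Table 3, "Vitamin D (>400 IU/day) or calcium (>1000 mg/day) supplementation".

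Two sources of information on vitamin D from outside the trial are collected:

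- Table 4 lists "Medication and supplement use" at baseline, 6 months and 12 months, under possible covariables.
- Serum 25(OH)D is measured at screening and 6 months. The Compliance section says: "The ultimate compliance check is the measurement of serum 25(OH)D after 6 months".

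The serum values have their own analyses under Data analysis. One is a compliance check on "the number of participants with serum 25(OH)D levels over 50, 60 and 75 nmol/L - will also be analysed in secondary analyses". The other relates change in 25(OH)D to change in the primary outcomes in the whole sample, with the arms pooled. Neither serum nor supplement use enters the per-protocol definition.

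**The concern.** Tablet count means different things in the two arms. In the vitamin D arm it measures exposure to the intervention. In the placebo arm it measures intake of inert tablets and says nothing about vitamin D. The stated rule therefore removes under-dosed participants from the active arm but cannot remove supplemented participants from the placebo arm.

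Over-cap use is foreseeable, because participants were selected for low 25(OH)D and own supplements are allowed up to a limit. A placebo participant who takes every tablet and also a substantial daily dose of vitamin D has moved some way towards active treatment, yet would be analysed as treated to plan.

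At stake is the reading of the per-protocol result. If it is null, it may be cited as showing no effect even when the supplement is taken as intended. The present definition does not fully support that statement.

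**Working it through.** **1. The two rules side by side.**

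| Participant | Non-study vitamin D rule (Intervention and randomisation) | Per-protocol rule (Data analysis) |
|---|---|---|
| At least 80 % of tablets, own vitamin D up to 400 IU/day | kept | included |
| Under 80 % of tablets | not relevant | removed |
| At least 80 % of tablets, own vitamin D above 400 IU/day | broken | included |

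The third row is the mismatch. Nothing elsewhere in the article removes that participant.

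**2. The plan's own figures.** Intervention and randomisation expects a mean 25(OH)D above 80 nmol/L on vitamin D and about 45 nmol/L on placebo, so a contrast of about 80 − 45 = 35 nmol/L. The power calculation uses a CES-D difference of 2.5 points, SD 5.1 and a baseline-to-follow-up correlation of 0.70. The SD of change is 5.1 × √(2 × (1 − 0.70)) = 3.95, which gives 40 per group at 80 % power and two-sided 5 %, as stated. The stated 22, 28 and 48 for the other primary outcomes reproduce in the same way. The sample size is not in question.

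**3. Dilution by over-cap use in the placebo arm.** Let c be the share of tablet-compliant placebo participants above the cap and d their daily non-study dose. The first 400 IU is permitted in both arms, so only the excess is charged to the breach. With serum and clinical effect assumed proportional to dose:

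attenuation = c × (d − 400) / 1200

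The documents give neither c nor d. The values below are assumptions.

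| c | d (IU/day) | Attenuation | 25(OH)D contrast, 35 × (1 − a) | CES-D difference, 2.5 × (1 − a) | Power, 40 per group | Power, 58 per group |
|---|---|---|---|---|---|---|
| 0 | – | 0 % | 35.0 | 2.50 | 0.81 | 0.93 |
| 5 % | 800 | 0.05 × 400/1200 = 1.7 % | 34.4 | 2.46 | 0.80 | 0.92 |
| 10 % | 1200 | 0.10 × 800/1200 = 6.7 % | 32.7 | 2.33 | 0.75 | 0.89 |
| 25 % | 1200 | 0.25 × 800/1200 = 16.7 % | 29.2 | 2.08 | 0.66 | 0.81 |

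Power is the normal approximation Φ(difference / (3.95 × √(2/n)) − 1.96). The 40 is the stated minimum for CES-D. The 58 is 155/2 × 0.75, the included sample after the expected 25 % dropout. Tablet non-compliance would bring the per-protocol set below 58 by an amount that the article does not give.

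**4. Direction.** Over-cap use in the placebo arm raises vitamin D exposure there and pulls the contrast towards zero. Over-cap use in the active arm is also counted as compliant and works the other way. The net effect is probably dilution but is not certain.

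**5. Can the other planned analyses stand in?** The serum threshold counts, shown by arm, would reveal supplemented placebo participants at 6 months. The 25(OH)D-change analysis uses actual status but pools the arms, so it is not a randomised comparison. Serum is not drawn at 12 months, when the primary outcomes are assessed, so use that starts after month 6 can show only in the 12-month supplement record. None of these changes who is in the per-protocol set.

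**The case against.** The strongest case against is that this is an optional refinement.

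- *The analysis is secondary.* This stands. No primary estimate, sample size or error rate depends on it.
- *The article may have shortened a longer list of deviations.* This stands only in part. The article does not leave the set open: it gives a numerical criterion, and the natural reading is that this is the definition.
- *The serum analyses already address actual exposure.* This stands in part. They soften the risk of misreading a null result, but they leave the set as it is.
- *The size is assumed, and the plan expects the placebo mean to stay near 45 nmol/L.* This stands. A reader might charge the whole 800-1200 IU to the breach and arrive at 3-25 % attenuation. The documents do not support that, because 400 IU/day is permitted.
- *Excluding over-cap users is itself selection.* This stands. People who start vitamin D may differ in mood or health behaviour, so removing them can shift the estimate in an unknown direction. A reader might infer that the present analysis is certain to be biased towards no effect. Neither this selection nor possible over-cap use in the active arm allows that certainty.
- *The data may not suffice.* This stands in part. Supplement use is recorded at each visit, but the article does not say that dose is recorded at follow-up, and two self-reports can miss use between visits.

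**Conclusion.** The point holds as a mismatch between a stated analysis set and the protocol's own rules. The per-protocol definition applies one of two adherence rules, and the one it omits is the one that protects the placebo arm. The likely consequence is some dilution of a secondary contrast. It would be about 2-17 % if 5-25 % of placebo participants take 800-1200 IU/day, effect is proportional to dose, only intake above the cap counts and no active-arm use offsets it. With no contamination rate in the documents, the true figure could lie outside that range and could be close to nil. Intention-to-treat results are untouched. The change is worth making because it is cheap and because it decides what a null per-protocol result may be taken to mean.

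**What to change.** Extend the per-protocol definition by one sentence: at least 80 % study-tablet intake, and reported non-study vitamin D not above the protocol's existing 400 IU/day cap at the follow-up visits with supplement data (6 and 12 months). With it:

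- apply the criterion identically in both arms and settle membership before unblinding;
- state how a missing visit, or a supplement reported without a dose, is handled;
- report the number excluded by arm and by criterion;
- show the tablet-only set alongside as a sensitivity analysis;
- keep intention-to-treat as the main analysis.

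This adds no dose or clinical rule; it applies the cap that the protocol already has. It uses a record that the trial already keeps, provided that dose can be recovered from it. The cost is a slightly smaller per-protocol set and some further selection after randomisation, of a kind that the tablet rule already brings.
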